### Primary outcome measures

#### Maternal

##### Pain relief

Measured using change in pain intensity from pre-analgesia levels over the subsequent 3 hours.

##### Pain relief at 60 minutes

Measured by change from baseline in pain intensity VAS at 60 minutes. The dose of analgesia is administered intra-muscularly, and it is anticipated that maximum analgesic effect will occur at around 60 minutes after administration. Pain intensity at 60 minutes was the primary outcome used by Fairlie et al [10], and is the basis of our sample size calculation.

#### Neonatal

##### Side effects

(a) Need for neonatal resuscitation

(b) Apgar Score <7 at 1 minute

### Secondary outcome measures

#### Maternal

##### Pain

(a) Verbal pain intensity over first 3 hours

(b) Verbal pain intensity at 60 minutes post administration

(c) Pain relief score over first 3 hours

(d) Maternal satisfaction with analgesia 12-24 hours after delivery

##### Other

(e) Maternal sedation score over first 3 hours

(f) Time from first dose to delivery

(g) Entonox or regional analgesia given

(h) Nausea over 3 hours

(i) Vomiting over 3 hours

(j) Oxygen saturation over 3 hours after each dose of study drug or until delivery

(j) Percent reporting that they would choose the same pain relief in their next pregnancy

#### Neonatal

(a) Cardiotocography over the first 3 hours after each dose of study drug or until delivery

(b) Time from first dose to first meconium staining

(c) Umbilical artery pH and vein pH

(d) Time from delivery to first breath

(e) Apgar score at 5 mins

(f) Requirement for naloxone

(g) Neonatal oxygen saturation at 30 mins, 60 mins, 90 mins, 120 mins after delivery

(h) Time from delivery to first feed

(i) Feeding behaviour during first 2 hours

(j) Neonatal sedation in the first 2 hours after delivery

(k) Transfer to neonatal intensive care unit

## Sample Size

The number of women to be recruited has been determined using a sample size calculation, and is based upon the maternal primary outcome measure of pain relief at 60 minutes, and the neonatal primary outcome measures of Apgar score < 7 at 1 minute and neonatal resuscitation. We could find no data on our specific maternal primary outcome on which to base the sample size calculation (i.e. change in pain intensity). However, Fairlie et al in their randomised trial of pethidine versus diamorphine [10] reported on VAS pain intensity at 60 mins post administration of the first dose, and we have based our sample size calculation upon this. A standard deviation (SD) for pain intensity post opiate administration can be estimated from the data they present (SD = 2.6), and we have estimated the SD of change in pain intensity using 3 scenarios of different correlations between post-analgesia and pre-analgesia scores; correlations of 0.3, 0.5 and 0.7 give SDs of 3.1, 2.6 and 2.0 respectively. A 1 cm difference on a 10 cm VAS represents 10% of the scale, and to detect mean differences of this magnitude between the two arms of the trial with 90% power (at the 5% significance level) will require sample sizes of 203, 144 and 86 per group respectively in the 3 scenarios. A 1 cm difference is similar to the difference in pain intensity at 60 minutes found by Fairlie (0.9), is not larger than the 1.4 cm identified by Holdgate et al [13] as being the minimum change in pain that can be subjectively identified by patients with acute pain, and represents a standardised effect size of 0.38. We will set sample size at the higher figure of 203 per group.

Regarding neonatal outcomes, the Fairlie trial found that around 30% of neonates required resuscitation, and that around 25% of neonates whose mothers were given pethidine had 1 minute Apgar scores of less than 7 [10]. Thus with 203 participants per group the study will have 90% power to detect reductions of around 50% in both these outcomes (i.e 30% v 16% and 25% v 12% respectively). The difference for Apgar scores is similar to that found by Fairlie et al [10].

Initially we will aim to recruit 450 to allow for the fact that not all women will have data on pain intensity, for example if they delivered soon after administration of the trial drug. However we will monitor this during the trial and alter our recruitment target accordingly.

The recruitment target will be split evenly between the 2 trial sites. In Poole there are approximately 4000 deliveries per year and at Royal United Hospital Bath there are approximately 3,500 (based on 2008 figures). Assuming a low recruitment rate of 10%, and taking into account that pethidine is currently administered to approximately 40% of women, recruitment should take around 24 months.

## Statistical Analysis

Women will be analysed in the group to which they were originally randomised, regardless of what subsequently occurred during their labour. To enable this, where appropriate, all measures will be collected on all women once they have been randomised. However, within this framework, women could still, at any time, withdraw their consent to be in the trial.

Data will be analysed using SPSS for Windows and MLWin [14]. Significance tests will use a 5% two-sided significance level. Randomisation will be stratified by study site, and this will be controlled for in all analyses. Given the design of the trial, it is anticipated that missing data will be mostly negligible. The exception will be for the observations taken at 30 minute intervals after administration of the trial drug, where observations will cease if the mother delivers. We will assume these missing data are "missing at random" [15]. Analysis of the two maternal primary outcome measures will be as follows. Pain relief will be measured at 30 minute intervals over 3 hours. The repeated measures nature of the data will be taken into account using a maximum likelihood based multi-level (mixed) model [14]. This model permits analysis of unbalanced repeated measures data thus avoiding exclusion of participants with incomplete data [14]. Initially the interaction between trial group and timing of pain VAS measurement will be tested to see if the effects of the study drug change over time. If the interaction effect is not statistically significant, the interaction will be removed from the multi-level model and the main effect of trial group tested. Parameter estimates with 95% confidence intervals will be presented. The second maternal primary outcome measure, mean difference in pain relief at 60 minutes, will be estimated using multiple regression.

The neonatal primary outcomes, need for resuscitation and Apgar score under 7 at 1 minute, will be compared between groups using logistic regression, and the results presented as odds ratios (95% CI) and Numbers Needed to Treat (NNT).

Supplementary analyses will adjust for the following covariates that might have an impact on primary outcomes: maternal age, parity, gestation, pre-administration pain intensity. No formal correction for multiplicity will be applied to the significance tests for the 4 primary outcomes. Under the null hypothesis that the two treatment groups give identical outcomes, the probablities of 1 or more, 2 or more, 3 or more, or all 4 being statistcally significant are 0.19, 0.01,<0.001 and <0.001 respectively. The trial report will include a section on the impact of multiplicity on interpretation of the results.

Analysis of secondary outcome measures is likely to be as follows. The distributions of oxygen saturation and nausea VAS are likely to be highly skewed and so values will be categorised. For example, as under 95, 95-97, 98-100 for oxygen saturation and 0, 0.1-4.9, 5+ for nausea. These and other repeated measures categorical outcomes (verbal pain intensity, pain relief, maternal sedation, vomiting, cardiotocography) will be analysed in two ways; (a) using repeated measures models, and (b) as the proportion of women having a poor result during the 3 hour follow-up, using logistic regression (eg proportions having oxygen saturation 97 or below, nausea 5+, verbal pain intensity moderate or worse, pain relief none or slight, sedation moderate or severe, vomiting, cardiotocography non-reassuring or abnormal). Neonatal oxygen saturation and sedation scores in the 2 hours after delivery will be analysed using a similar approach.

Maternal satisfaction with analgesia and neonatal feeding behaviour (normal, mildly depressed, severely depressed) will be analysed using multinomial logistic regression.

Dichotomous outcomes such as Apgar score < 7 at 5 minutes, use of naloxone, transfer to neonatal intensive care unit, and reporting that they would choose the same analgesia for their next pregancy, will be analysed using logistic regression.

Time from first administration of study drug to delivery, and time to first meconium staining (excluding those where staining ocurred prior to trial drug), and time from delivery to first feed and time to first breath will be analysed using proportional hazards models, and the results presented as hazard ratios.

Multiple regression will be used to analyse umbilical artery pH and vein pH. Results will be presented with 95% confidence intervals whenever possible.

Both trial drugs are widely used in the NHS and internationally. No interim analysis is planned, but will be conducted if specifically requested by the trial Data and Safety Monitoring Committee. The main role of the DSMC will be to monitor serious adverse events.

Results will be reported using CONSORT guidelines [16].

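### The 3-hour pain primary has a data-dependent two-step test with no stated success criterion: either its false-positive rate is about 9.75%, or it has no overall treatment test when the interaction is significant

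*Protocol article*

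**What the plan says.** Under Primary outcome measures, the Protocol article defines the first maternal primary thus: "Measured using change in pain intensity from pre-analgesia levels over the subsequent 3 hours". Statistical Analysis gives the schedule, "Pain relief will be measured at 30 minute intervals over 3 hours", which makes six post-dose readings (30 to 180 minutes).

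The test has two steps. The first is this: "the interaction between trial group and timing of pain VAS measurement will be tested to see if the effects of the study drug change", meaning from one reading to the next. The second is conditional: "If the interaction effect is not statistically significant, the interaction will be removed from the multi-level model". Only in that case is the overall comparison made, in the words "and the main effect of trial group tested". No separate level is given for either step, so the general rule applies: "Significance tests will use a 5% two-sided significance level". For reporting, the section says "Parameter estimates with 95% confidence intervals will be presented". It names no summary effect or test for the case of a significant interaction.

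The same section declines a multiplicity correction for the four primaries. It gives null probabilities of 0.19 for at least one significant result and 0.01 for at least two.

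The 60-minute difference is a separate primary, estimated by multiple regression. Of its timing the protocol says "it is anticipated that maximum analgesic effect will occur at around 60 minutes after administration".

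**The concern.** Whether the main comparison for a primary outcome is made at all depends on a preliminary test on the same data, and the rule does not say what counts as success. The two possible readings fail differently:

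- **Reading A: a significant result at either step is positive.** The outcome gets two chances at 5%, while the published multiplicity figures count it once. A significant interaction across six readings also has no direction, so it does not show which drug relieves pain better over 3 hours.
- **Reading B: only the group effect is positive.** The error rate is controlled, but a significant interaction leaves the 3-hour outcome without an overall treatment comparison.

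On neither reading does this primary have one pre-specified 5% test that is always carried out. At stake is whether a claim about 3-hour pain relief can be read at its stated error rate, or made at all.

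**Working it through.** **Inputs from the Protocol article.** Statistical Analysis: 5% two-sided for each test, six post-dose readings, four primaries. Sample Size: 203 women per group, SD of change 3.1 cm (the largest of its three scenarios), difference of 1 cm.

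**1. The plan's own figure.** With four independent 5% tests, 1 − 0.95⁴ = 0.1855, which rounds to the stated 0.19. The probability of two or more is 0.0140, the stated 0.01. Both reproduce, with one 5% test per primary.

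**2. Reading A.** The interaction and group tests are taken as independent under the null.
- This outcome: 1 − 0.95² = 0.0975.
- At least one of the four primaries: 1 − (0.9025 × 0.95³) = 1 − 0.95⁵ = 0.226, against 0.1855.

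**3. Reading B.** 0.95 × 0.05 = 0.0475.

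**4. Check by simulation under the null.** There were 4,000 trials per scenario, with compound-symmetry or AR(1) correlation of 0.3 to 0.7 and no loss or 15% loss of women per interval (assumed).
- Reading A: 0.095 to 0.104 with time categorical (5 df), 0.093 to 0.105 with time linear.
- Reading B (time categorical): 0.045 to 0.053.
- One time-averaged contrast: 0.046 to 0.055.

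**5. How often the group test is not reached.** The protocol gives no between-drug difference at any time other than 60 minutes, so the profiles below are assumptions. Settings: SD 3.1, 203 per group, 15% loss per interval, time categorical, 1,500 trials each. Ranges cover compound symmetry at 0.5 and AR(1) at 0.7.

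| Assumed difference at 30, 60, 90, 120, 150, 180 min (cm) | Interaction significant | Group test reached and significant | Averaged contrast significant |
|---|---|---|---|
| 1, 1, 1, 1, 1, 1 | 5–6% | 92–93% | 97% |
| 0.5, 1, 0.9, 0.8, 0.6, 0.5 | 24–33% | 50–62% | 79–80% |
| 0.4, 1, 1, 0.7, 0.4, 0.2 | 53–54% | 28–32% | 64–67% |
| 0, 1, 1, 0.5, 0, 0 | 93–94% | 1–2% | 36% |

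**6. Sensitivity.** Two similar profiles were examined at SD 2.6 to 3.1 and correlation 0.4 to 0.6: a peaked one (0.4, 1.0, 0.9, 0.6, 0.4, 0.2 cm) and a flatter one (0.5, 1, 1, 0.8, 0.6, 0.5 cm). The interaction is significant in:
- complete data, compound symmetry: 60–93% (peaked) and 35–69% (flatter);
- complete data, AR(1): 39–69% and 24–45%;
- 15% loss per interval: 40–76% and 25–51%;
- 25% loss per interval: 31–61% and 21–41%.

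The form of time matters too. If time is linear, the interaction in the three time-varying rows of the table is significant in only 6–14% of trials, because a rise and fall is poorly captured by a slope. The article does not state the form.

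**The case against.** The strongest reply is that the interaction test reads as diagnostic. Its stated purpose is to see whether drug effects change over time, and nothing calls a significant interaction a success. On that reading there is no inflation and the 0.19 stands. This is fair, and it means the 0.0975 and 0.23 are conditional. It does not rescue the rule, because the same reading leaves the 3-hour outcome without an overall test when the interaction is significant.

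A reader might infer four stronger things, none of which the document supports:

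- **That both harms occur together.** They need opposite readings. If a significant interaction counts there is a test, and if it does not count the error rate is not inflated.
- **That the protocol expects a significant interaction.** It expects analgesic effect to peak near 60 minutes. A peak shared by both drugs is an effect of time, not of group-by-time. A varying difference is plausible but is an inference.
- **That the trial would be left with no pain result.** The 60-minute primary is analysed regardless and carries the maternal sample size, and estimates with confidence intervals are promised. It is a different outcome, though, and cannot stand in for the 3-hour one.
- **That time points would be picked after seeing the data.** The protocol fixes 60 minutes in advance, and nothing in it points to such a choice.

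It can also be said that a condensed article may leave the handling of a significant interaction to a fuller document. That is true of the detail. The gate itself is written down as the rule for a primary outcome, so a later document would have to overturn it, not just complete it. Finally, the protocol is open about multiplicity and promises to discuss it. That stands, but its figures allow one test for this outcome.

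**Conclusion.** The point holds as an either/or. If either step counts, the false-positive rate for the 3-hour primary is about 0.0975 instead of 0.05, and the published 0.19 becomes about 0.23. If only the group effect counts, the rate is about 0.0475, but there is no overall 3-hour treatment test whenever the interaction is significant. The document does not say which applies.

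The error rates rest on independence of the two steps, which the simulation bears out. The 0.23, like the protocol's 0.19, also treats the four outcomes as independent.

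The frequency of a missing test is much less certain. With time categorical it is about 5% for a constant difference, and roughly a quarter to over 90% for the assumed time-varying profiles, with 21% as the lowest value under the heaviest loss examined. These figures illustrate the exposure and do not predict it.

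**What to change.** Replace the two-step rule with one test. Fit the multi-level model with group, categorical time, group-by-time and site, and keep group-by-time in whatever its p-value. The primary test is that the mean of the six time-specific group differences is zero, at 5% two-sided. Report the interaction and the time-specific differences with 95% confidence intervals as supportive only. Decide this before unblinding.

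This gives the outcome one 5% test and leaves the 0.19 valid. Adjustment for pre-administration pain is not needed for it and can stay among the supplementary analyses, where the protocol puts it.

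The cost is about two sentences of text, with the same type of model. If the difference is truly constant at 1 cm, precision is slightly lower than in the no-interaction model: simulated power is about 97% against 98% for an ungated group test. An equal average is also weak against a short-lived difference (36% in the last row of the table). In that setting the 60-minute comparison, already a primary, had simulated power of 85–89%.

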## Measurements

• *General demographics*. Age, weight, gestational age, cervical dilatation at first request for analgesia, frequency of contractions, parity, spontaneous or induced labour, use of syntocinon, presentation, mode of delivery, drug administration to delivery interval. This information will be derived from the maternal notes and interview with the midwife taking care of the parturient.

• *Maternal Pain Evaluation*. Pain severity during last contraction will be assessed using a visual analogue score (VAS) (with anchor points of 0 = no pain at all and 10 = the most excruciating pain) and verbal scales of pain intensity during the last contraction (pain intensity score: 0 = no pain; 1 = mild pain; 2 = moderate pain; 3 = severe pain). In addition, the midwife will assess pain relief during the previous 30 minutes (pain relief score: 0 = none; 1 = slight; 2 = moderate; 3 = good, 4 = complete).

• *Maternal Sedation and Vomiting Evaluation*. Maternal sedation during the previous 30 minutes will be assessed by the midwife using sedation scores (0 = alert; 1 = mild i.e. occasionally drowsy and easily aroused; 2 = moderate sedation i.e. frequently drowsy but still easily aroused; 3 = severe sedation i.e. somnolent and difficult to rouse) and by measuring maternal oxygen saturation by pulse oximetry. Maternal pulse oximetry measurement is integral within the cardiotocograph (CTG) machine (Phillips PN/2703A) at the RUH and using the Masimo Rad 5 machine at PHFT. Vomiting will be assessed as a side effect with a yes/no answer pre-dose and during each subsequent thirty minutes period.

Maternal assessments will be made when the woman first requests analgesia and then every thirty minutes after the trial drug has been given, for a maximum of three hours or until delivery has occurred or additional analgesia is requested. A further 3 hours of measurements are then made if additional opioid analgesia is requested not less than 2 hours after the first dose. The parturient's overall satisfaction with the analgesia will also be assessed 12-24 hours post partum as well as their wish to choose the same opioid for their next labour analgesia.

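### As written, the 60-minute primary outcome is a regression on women with a 60-minute score only, although the plan uses a likelihood model on the same series to avoid such exclusion

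*Protocol article*

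**What the plan says.** The Protocol article has two maternal primary outcomes built on the same half-hourly VAS series, and the Statistical Analysis section gives each its own method.

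- 3-hour outcome: "The repeated measures nature of the data will be taken into account using a maximum likelihood based multi-level (mixed) model". The reason given is: "This model permits analysis of unbalanced repeated measures data thus avoiding exclusion of participants with incomplete data".
- 60-minute outcome: "The second maternal primary outcome measure, mean difference in pain relief at 60 minutes, will be estimated using multiple regression". No imputation or other handling of absent scores is mentioned.

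Before naming either method, the section says the half-hourly scores are the one place where appreciable missing data are expected, and assumes them to be missing at random. The only cause it names is delivery: "where observations will cease if the mother delivers". The Measurements section is wider. There, assessments run "for a maximum of three hours or until delivery has occurred or additional analgesia is requested".

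The Sample Size section bases the maternal calculation on the 60-minute outcome (203 per group) and adds: "Initially we will aim to recruit 450 to allow for the fact that not all women will have data on pain intensity". The abstract likewise expresses the requirement as 406 women who have primary-outcome data.

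**The concern.** The 60-minute VAS is one point of the series that the mixed model already analyses. A regression of 60-minute change on group and site drops every woman without that score and ignores her 30-minute score if she has one. The requirement of 406 women with data, against 450 recruited, fits that reading.

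The two analyses then treat the same missing scores differently. The likelihood model is valid when stopping depends on scores already observed, such as pain at 30 minutes. The regression never uses the 30-minute score, so it generally needs a stricter condition. The Measurements section makes the difference matter: asking for more analgesia ends assessment and is plausibly driven by pain.

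At stake is the estimate of the outcome that sizes the trial. If one drug relieves pain better, which is what the trial sets out to test, the women lost before 60 minutes may differ between arms in number or in reason.

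**Working it through.** **1. The plan's sample size.** Inputs from Sample Size: post-dose SD 2.6, difference 1 cm, 90% power, 5% significance (two-sided, from Statistical Analysis).

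- SD of change = 2.6 × √(2(1 − r)) = 3.08, 2.60 and 2.01 for r = 0.3, 0.5 and 0.7. The plan states 3.1, 2.6 and 2.0.
- The t-based sample size for those stated SDs, rounded up, is 203, 144 and 86 per group, as stated.

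The stated figures reproduce, so this is not a sample-size error.

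**2. What recruiting 450 buys.** The allowance is 450 − 406 = 44, and 44/450 = 9.8%. Power ≈ Φ(1/(3.1 × √(2/n)) − 1.96), with n = 225 × (1 − proportion missing) per arm:

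| Missing at 60 min | n per arm | Power |
|---|---|---|
| 0% | 225 | 92.8% |
| 5% | 213.75 | 91.5% |
| 9.8% | 203 | 90.1% |
| 20% | 180 | 86.4% |
| 30% | 157.5 | 81.7% |

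Power is protected up to about 10% missing. The protocol gives no expected rate; the rows other than 9.8% are assumptions.

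**3. Selection.** This was checked by simulation with 225 per arm and 3000 runs. The SD is 2.6 and the true difference is 1.0 cm at 30 and at 60 minutes. Assumptions not in the protocol: correlation 0.7 between the 30- and 60-minute scores, correlation 0.3 with baseline, and stopping after the 30-minute score. Where stopping is pain-driven, its log-odds rise by 0.5 per cm of 30-minute pain. The comparator is a likelihood-type estimate of the 60-minute contrast that uses the baseline and 30-minute scores.

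| Stopping before 60 minutes | Complete-case regression (cm) | Likelihood-type contrast (cm) |
|---|---|---|
| Pain-driven, same rule in both arms, 5% overall | 0.97 | 0.99 |
| Same rule, 10% overall | 0.96 | 1.00 |
| Same rule, 20% overall | 0.94 | 1.00 |
| Pain-driven, 9.8% in each arm | 0.99 | 1.00 |
| 10% in each arm, pain-driven in one, unrelated to pain in the other | 0.88 | 0.99 |
| Pain-driven in both, 15% versus 5% | 0.89 | 1.00 |
| 20% pain-driven versus 10% unrelated | 0.78 | 1.00 |

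A stopping rule common to both arms costs nothing to about 6% of the effect. Rates or reasons that differ by arm cost roughly 10 to 20%. In these runs the arm with more pain-driven loss was the one with more pain; the direction reverses if that is swapped. If scores are missing completely at random, neither method is biased.

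**4. Precision.** With 9.8% missing completely at random, the standard error is 0.310 for complete cases and 0.301 for the likelihood-type contrast, a small gain. Baseline adjustment matters more. With r = 0.3 and 203 per arm:

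- Change score: SE = 3.08 × √(2/203) = 0.305.
- Baseline-adjusted: SD = 2.6 × √(1 − 0.3²) = 2.48, so SE = 2.48 × √(2/203) = 0.246.

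With r = 0.7 the same formulas give 0.200 and 0.184, so this gain shrinks as the baseline correlation rises. Adding baseline to the complete-case regression would capture most of the precision but would not remove the selection, because the 30-minute score would still be unused.

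**The case against.** **The exclusion is inferred.** The section names an estimator and does not say complete case. Its missing-at-random statement precedes both analyses and can be read as covering both, and an SAP not shown might add imputation. This stands as a limit on wording. But the protocol does fix the method for this outcome, and gives avoidance of exclusion as the reason for choosing a different method on the same data.

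**The loss was foreseen.** Recruitment is raised to 450, the shortfall is to be monitored and the target can be altered. This stands for power and does not touch selection.

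**Early stopping may be rare.** A second trial dose requires an interval of at least two hours (Allocation of analgesia), so before 60 minutes only requests for other analgesia could end assessment. The larger biases rest on assumed differences between arms. Both points stand. If stopping depends on pain that was never recorded, the likelihood model is not protected either.

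**A likelihood contrast answers a different question.** A woman who has delivered has no labour pain at 60 minutes. The regression describes women still under assessment; the model supplies a value as if labour had continued. This stands and has to be stated in the plan.

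Three stronger readings are tempting but not supported:

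- A reader might infer a breach of the rule that women are analysed as randomised. That rule governs which arm a woman counts in, and a missing score moves nobody between arms.
- A reader might infer that about 22 lost women could be recovered (44 × 0.7² = 21.6). That is an upper bound, since it needs a 30-minute score for every one of the 44. The plan's own example is women who deliver soon after the dose, and some of these will have no post-dose score.
- A reader might infer that the change is free because the model is already planned. The planned model drops a non-significant group-by-time term, and baseline pain is reserved for supplementary analyses.

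**Conclusion.** The point holds as an avoidable weakness in the analysis of the outcome that sizes the trial. As written, the 60-minute regression uses only women with a 60-minute score, under a stricter missing-data condition than the one the plan states, while a better-suited method is already applied to the same series. The sample size is correct, and 450 recruits give about 90% power at about 10% missing.

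The remaining risk is selection: nil to about 6% of a 1 cm effect under a common stopping rule, and roughly 10 to 20% if rates or pain-related reasons differ by arm. These sizes depend on the assumed correlations, drop-out slope and rates; the protocol gives no rates by reason. The precision argument alone would not justify using the 30-minute scores, because most of that gain comes from baseline adjustment.

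**What to change.** In Statistical Analysis, define the 60-minute difference as the time-specific contrast from a maximum-likelihood repeated-measures model. Use categorical time, keep the group-by-time term for this contrast whatever its significance, and include baseline VAS and site as covariates. Keep the complete-case regression as a sensitivity analysis.

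State the estimand: for women who deliver before 60 minutes, the contrast is a model-based value had labour continued. Note also that a woman with no post-dose score contributes little or nothing to this model. Reconcile the reasons for stopping assessment in Measurements (delivery or a request for additional analgesia) with those in Statistical Analysis (delivery only), so that the missing-at-random assumption is stated for the data that will actually be absent.

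The cost is a small respecification of the planned model and an explicit estimand statement. Baseline pain moves from the supplementary analyses into the primary one for this outcome. No new data, software or recruitment is needed.

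### The primary pain analyses leave baseline pain to supplementary models, so they are valid but less precise than the same data allow

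*Protocol article*

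**What the plan says.** Both maternal primary outcomes in the protocol article are change scores. The 3-hour outcome is "Measured using change in pain intensity from pre-analgesia levels over the subsequent 3 hours" and the 60-minute outcome is "Measured by change from baseline in pain intensity VAS at 60 minutes".

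Under Statistical Analysis, the 3-hour outcome goes into a multilevel model: "The repeated measures nature of the data will be taken into account using a maximum likelihood based multi-level (mixed) model". For the 60-minute outcome the article states: "The second maternal primary outcome measure, mean difference in pain relief at 60 minutes, will be estimated using multiple regression". One covariate is fixed for every analysis: "Randomisation will be stratified by study site, and this will be controlled for in all analyses". Pre-dose pain is named later in the same section, among the supplementary adjustments: "Supplementary analyses will adjust for the following covariates that might have an impact on primary outcomes: maternal age, parity, gestation, pre-administration pain intensity".

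Sample Size takes a post-dose SD of 2.6 and derives the SD of change under three scenarios: "correlations of 0.3, 0.5 and 0.7 give SDs of 3.1, 2.6 and 2.0 respectively". A 1 cm difference at 90% power and 5% significance then needs 203, 144 or 86 per group, and the largest figure is adopted. The same 203 is used for the two neonatal primary outcomes.

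**The concern.** A change score subtracts the whole of the baseline value, whatever the correlation between pre-dose and post-dose pain. When that correlation is modest, much of what is subtracted is noise with respect to the later score. Regression on baseline subtracts only the part that predicts the later score, so in large samples its variance is no larger than that of the change score, and is usually smaller.

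The trial records pre-dose VAS and already names it as a covariate, yet the headline estimate does not use it that way. Two things follow. The primary confidence interval for pain is wider than it need be. And if the unadjusted and adjusted results fall on different sides of 5%, the less precise one is the primary result.

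**Working it through.** **Inputs** (protocol article, Sample Size and Statistical Analysis): post-dose SD 2.6 cm; correlation r = 0.3, 0.5, 0.7; difference 1 cm; power 90%; two-sided 5%; 203 per group.

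**Step 1: reproduce the plan.** With equal SDs before and after dosing, SD of change = 2.6 × √(2(1−r)). This gives 3.08, 2.60 and 2.01, matching the stated 3.1, 2.6 and 2.0, so equal SDs are the plan's own implicit assumption. A t-based two-sample calculation with the rounded SDs returns 203, 144 and 86 per group, exactly as stated. With the unrounded SDs it gives 200, 144 and 87.

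**Step 2: adjust for baseline.** The residual SD after regression on baseline is 2.6 × √(1−r²). The ratio of the two variances is (1−r²) / (2(1−r)) = (1+r)/2.

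| r | SD of change | Adjusted SD | Variance ratio | n per group for 90% power, change → adjusted | Power at 203 per group, change → adjusted |
|---|---|---|---|---|---|
| 0.3 | 3.08 | 2.48 | 0.65 | 200 → 131 | 90.4% → 98.2% |
| 0.5 | 2.60 | 2.25 | 0.75 | 144 → 108 | 97.2% → 99.4% |
| 0.7 | 2.01 | 1.86 | 0.85 | 87 → 74 | 99.9% → 99.97% |

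Standard error at r = 0.3 with 203 per group: 3.076 × √(2/203) = 0.305 cm for change and 2.480 × √(2/203) = 0.246 cm adjusted. The difference detectable with 90% power falls from 0.99 to 0.80 cm.

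At r = 0.3 the SD of change (3.08) also exceeds the SD of the raw 60-minute score (2.6), so subtracting baseline is then worse than ignoring it. At r = 0.5 the two are equal, and at r = 0.7 the change score has the smaller SD.

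**Step 3: chance imbalance.** Suppose the groups differ by d in mean baseline pain. Under equal SDs, the expected difference in change (post minus pre) is the treatment effect plus (r−1)d. The change score over-corrects: an error of (1−r)d remains, in the direction opposite to the imbalance. That is 70%, 50% or 30% of d in the three scenarios. At r = 0.3 an imbalance of one standard error, 2.6 × √(2/203) = 0.26 cm, shifts the estimate by 0.7 × 0.26 = 0.18 cm. Baseline adjustment removes this.

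**Step 4: sensitivity to the baseline SD.** The article gives no pre-dose SD, so the values s below are assumptions. Variance of change = 2.6² + s² − 2r × 2.6 × s; adjusted variance = 2.6²(1−r²). At r = 0.3:

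- s = 1.3: ratio 0.958, about 4% lower
- s = 2.0: ratio 0.805, about 20% lower
- s = 2.6: ratio 0.65, 35% lower
- s = 3.0: ratio 0.555, about 45% lower

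At some combinations (s = 1.3 with r = 0.5, for example) the ratio is 1.0 and there is no gain.

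**Step 5: can n be reduced?** The neonatal comparisons, 30% v 16% and 25% v 12% at 90% power, need 188 and 186 per group without continuity correction, or 202 and 201 with it. At 132 per group (203 × 0.65) their power would be about 77% and 78%.

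**The case against.** The best defence is that nothing here is invalid. Change from baseline is unbiased under randomisation, matches the stated outcomes and matches the basis of the sample size. The adjusted estimate will be produced anyway as a supplementary analysis. At r = 0.5 or 0.7 the change score already has 97% power or more, so adjustment adds little power there. All of this stands. It makes the point one of precision, but gives no reason to keep the less precise analysis as primary.

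It might also be said that multiple regression at 60 minutes could already include baseline pain. The text does not support that reading: site is the only covariate named for all analyses, and listing pre-dose pain as a supplementary adjustment would then be redundant.

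Three stronger conclusions are tempting and are not supported:

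- **That a third of the sample is wasted.** A reader might infer this from 131 against 203. But the sample size also serves the neonatal primary outcomes, which need about 200 per group with continuity correction. No women would be saved.
- **That the change score carries a baseline imbalance in full.** Under the plan's assumptions it leaves (1−r) of it, with reversed sign. The full amount would remain only at r = 0.
- **That the gain is 35% for both maternal outcomes.** That figure belongs to the most cautious of three scenarios, assumes equal SDs, and applies to the 60-minute outcome only. The gain in the 3-hour model depends on within-woman correlations that the article does not give.

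**Conclusion.** The point holds as a loss of precision, not of validity. For the 60-minute outcome, with equal pre-dose and post-dose SDs of 2.6, adjustment lowers the variance by 35%, 25% or 15% at r = 0.3, 0.5 or 0.7. In the scenario that sets n, that means power of about 98% instead of 90% for 1 cm. The size is uncertain because the baseline SD is not given: a value below 2.6 makes the gain smaller, down to nothing at some combinations. The direction is secure, since in large samples adjustment does no worse. For the 3-hour outcome only the direction can be stated. The change is worth making because it has no real downside, and the extra margin helps if fewer than 406 women provide pain data, a risk that the article itself raises.

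**What to change.** Before any unblinded outcome data are seen, make the baseline-adjusted model primary for both maternal outcomes:

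- At 60 minutes, regress change (or VAS) on group, site and pre-dose VAS. Both give the same treatment effect, because subtracting baseline from the response only lowers the baseline coefficient by 1. The outcome definition can therefore stay as it is.
- Over 3 hours, add pre-dose VAS as a covariate in the multilevel model.
- Keep the change analysis without baseline adjustment as supplementary. Maternal age, parity and gestation can stay supplementary.
- Keep 203 per group.

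The cost is a sentence or two in Statistical Analysis. No new data or participants are needed: pre-dose VAS is already recorded, and a woman without it would have no change score either.
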